## Abstract

**Background:**

Knee osteoarthritis (OA) is a leading cause of chronic pain and disability. With projections indicating 642 million affected individuals globally by 2050, identifying safe, scalable, and potentially disease-modifying non-pharmacological interventions is an urgent public health priority. This study aims to compare the clinical effectiveness of Tai Chi, Baduanjin, and a health-education programme in preserving joint function and quality of life for patients with knee OA.

**Methods/design:**

A single-centre, 48-week, comparative-effectiveness randomised controlled trial comparing Tai Chi, Baduanjin and health-education programme will be conducted at Zhongshan Hospital of Traditional Chinese Medicine. Eligible participants consists of adults ≥60 years of age with symptomatic and radiographic knee OA. Participants will be randomly assigned (1:1:1) using a computer-generated randomization sequence to one of three groups: (1) Tai Chi training, 5 sessions per week (60 min each) for 12 weeks; (2) Baduanjin training, 5 sessions per week (60 min each) for 12 weeks; or (3) health-education, 1 session per week (60 min each) for 12 weeks. Outcome assessors will be blinded to group allocation. The primary outcomes are the pain, stiffness and physical function subscales of the Western Ontario and McMaster Universities Osteoarthritis Index (WOMAC). Secondary outcomes include the Berg Balance Scale, 6 min walk test and SF-36 quality-of-life assessment. All measures will be assessed at weeks 12, 24 and 48.

**Discussion:**

By comparing two traditional mind-body exercises against an active control group over 48 weeks, this trial is designed to determine whether these interventions offer durable clinical benefits as standalone therapies or provide additive value. The findings are expected to provide high-quality evidence regarding scalable, low-cost non-pharmacologic strategies for managing knee OA, with potential implications for public health policy.

**Clinical Trial Registration:**

International Traditional Medicine Clinical Trial Registry (ITMCTR), http://itmctr.ccebtcm.org.cn/, identifier ITMCTR2025000409.

## Background

Knee osteoarthritis (KOA) is now the leading cause of global musculoskeletal disability, characterised by chronic pain, progressive functional decline and impaired quality of life (1). The Global Burden of Disease Study 2021 estimated that 595 million people worldwide had symptomatic osteoarthritis in 2020, and projections indicate a 74.9% increase in cases by 2050 compared with 2020, driven predominantly by population ageing and rising obesity (2). In economic terms, recent Nordic-wide registry data from the BISCUITS study show that the total annual incremental societal cost attributable to osteoarthritis—comprising direct medical expenditures and indirect productivity losses—averaged €3,224–4,969 (≈US$ 3,600–5,500) per patient in 2017 (3). Hence, safe, scalable and cost-effective non-pharmacological interventions are now an international priority (4).

Current pharmacological options for knee osteoarthritis exert only modest and transient symptom relief; non-steroidal anti-inflammatory drugs and acetaminophen frequently provide insufficient analgesia, while their chronic use is associated with appreciable gastrointestinal, renal and cardiovascular harms (5–7). Tai Chi and Baduanjin are increasingly recommended mind-body exercises for knee osteoarthritis. Although accumulating trials report symptomatic and functional benefits, heterogeneity in training parameters precludes definitive conclusions regarding their comparative effectiveness or superiority over structured health education (8–10).

Consequently, developing safe, scalable and evidence-based non-pharmacological strategies to enhance and sustain physical function and quality of life in individuals with knee osteoarthritis is now widely recognized as a high-priority research area, as emphasized in recent OARSI and EULAR guidelines for the non-surgical management of knee OA (11, 12).

While high-quality evidence underscores aerobic exercise as a cornerstone treatment for KOA due to its efficacy in improving cardiopulmonary function and weight management (13), this study prioritizes Tai Chi and Baduanjin for three critical reasons specific to the target demographic and holistic care goals. First, unlike pure aerobic regimens, these mind-body exercises integrate physical movement with mental regulation and breath control, offering unique dual-task benefits. Evidence suggests they provide additional advantages in improving balance (thereby reducing fall risk), enhancing psychological well-being, and developing pain coping mechanisms, which are vital for the comprehensive management of chronic KOA (14). Second, adherence is a pivotal challenge in exercise therapy for older adults. For the specific population affected by KOA—often characterized by fear of falling or limited mobility—mind-body exercises frequently demonstrate higher long-term adherence rates compared to strenuous aerobic protocols (15). Finally, given our research focus on Traditional Chinese Medicine (TCM) non-pharmacological therapies, investigating these culturally embedded practices is essential. They represent scalable, community-based interventions that are readily accepted by the aging population in Asia and are gaining global recognition.

Previous research has established that Tai Chi—an integrative mind-body modality that harmonizes deep diaphragmatic breathing, progressive relaxation, and deliberate yet graceful physical maneuvers—exerts beneficial effects on the health profiles of individuals with chronic diseases (14, 16, 17). Empirical evidence has documented substantial enhancements across a range of domains, including equilibrium, muscular strength, cardiopulmonary efficiency, physiological flexibility, pain mitigation, mood states, and attenuation of arthritis-related manifestations (18–20).

Recent studies have highlighted the therapeutic potential of Baduanjin in alleviating symptoms of osteoarthritis. By promoting fluid circulation within the joints and stimulating the surrounding musculature, Baduanjin can reduce stiffness and pain, thereby improving overall joint function (21, 22). Moreover, its low-impact nature minimizes the risk of further joint damage, making it a safe and accessible option for patients. Preliminary findings suggest that regular practice of Baduanjin can lead to significant improvements in physical function and quality of life for those affected by osteoarthritis, positioning it as a promising complementary therapy in the management of this chronic condition (23–25).

Hence, we are presently conducting a comparative efficacy and cost-effectiveness trial within a substantial cohort of patients with symptomatic knee OA.We propose that Baduanjin may offer distinct advantages over routine health education commonly delivered in clinical practice. Additionally, we seek to evaluate the comparative merits of Tai Chi in this context. Our overarching goal is to elucidate whether Baduanjin and Tai Chi can effectively reduce pain and functional limitations associated with knee OA, thereby enhancing the quality of life for individuals affected by this condition.

In this article, we outline the design and comprehensive protocol for the first three—arm randomized controlled trial comparing the clinical effectiveness and cost—effectiveness of Tai Chi, Baduanjin, and a health—education program in older adults with knee OA. We anticipate that this study will bridge significant knowledge gaps and provide valuable evidence to guide clinical practice and policy decisions related to the management of knee OA. The findings will be disseminated upon study completion, adhering to the Consolidated Standards of Reporting Trials (CONSORT) guidelines (26).

## Methods/design

### Study design overview

This investigation is a single—center, 48-week randomized controlled trial (Figure 1). Study flow diagram). The design and reporting of this study protocol adhere to the Standard Protocol Items: Recommendations for Interventional Trials (SPIRIT) guidelines. A total of 120 older adults with symptomatic knee osteoarthritis will be randomly allocated to one of three groups: Tai Chi training (5 sessions per week for 12 weeks), Baduanjin training (5 sessions per week for 12 weeks), or a health-education program (1 session per week for 12 weeks), with 40 participants in each group.

**Figure 1 F1:**
[figure not shown]
Study flow diagram.

The primary outcomes encompass the pain, stiffness, and physical function subscales of the Western Ontario and McMaster Universities Arthritis Index (WOMAC) (27). Secondary outcomes will be assessed using the Berg Balance Scale, which evaluates balance performance through a series of functional tasks; the 6-minute walk test, which measures endurance and mobility by assessing the distance walked in 6 min; and the Health Survey Short Form (SF-36), a comprehensive questionnaire that assesses overall health-related quality of life across multiple domains. These measures will provide a holistic view of the participants' physical and psychosocial well-being. Outcome measurements will be conducted at baseline, immediately following the 12-week intervention period, and at 24 and 48 weeks to assess the durability of treatment effects. The personnel administering the physical function evaluations and the data analyst are unaware of the participants' treatment allocations. The specific endpoints and their categorization as outcomes are detailed in Table 1.

**Table 1 T1:** Schedule of assessments for primary and secondary outcomes.

Time	Baseline	Week 12	Week 24	Week 48
Primary Outcome variables				
WOMAC^a^—Pain	×	×	×	×
WOMAC—Physical Function	×	×	×	×
WOMAC—Stiffness	×	×	×	×
Secondary outcome variables				
SF-36^b^	×	×	×	×
Berg Balance Scale^c^	×	×	×	×
6 min walk test^d^	×	×	×	×

a WOMAC: Western Ontario and McMaster Universities Osteoarthritis Index.

b SF-36: Medical outcome survey short-form 36.

c Berg Balance Scale: A 14-item test that measures a person's balance and walking abilities.

d 6 min walk test: A simple test that measures how far a person can walk in six minutes.

The study setting is the Zhongshan Hospital of Traditional Chinese Medicine, affiliated with Guangzhou University of Traditional Chinese Medicine, located in Zhongshan, Guangdong, China. The study received ethics approval from the Institutional Review Board of Zhongshan Hospital of Traditional Chinese Medicine.

## Study status and timeline

As of the date of manuscript submission, participant recruitment has not yet begun. Recruitment is expected to commence in January 2026, with an estimated completion by June 2026. Data collection is anticipated to conclude by mid-2027, and the final results are expected to be available for analysis by late 2027. No data have been analyzed or reported at this stage.

### Study sample

The inclusion criteria for this study are as follows: Participants must be aged 60 years or older and have experienced pain symptoms for at least three months. They must be patients with mild to moderate osteoarthritis, as evidenced by a Western Ontario and McMaster Universities Osteoarthritis Index (WOMAC) pain subscale score ranging from 13 to 38 points (on a 0–50 points scale). Additionally, participants must have a total WOMAC score ranging from 50 to 150 points (on a 0–240 points scale) (28). Participants must be cognitively intact, with the ability to communicate effectively through writing or speech. They should also be able to walk independently without the use of assistive devices and be capable of performing a moderate amount of exercise on their own. Finally, participants must voluntarily agree to take part in this study and provide informed consent.

Participants will be excluded if they have any of the following: (1) prior experience with Tai Chi, Qigong, yoga, or similar exercises, or physical therapy for knee osteoarthritis within the past year; (2) severe medical conditions such as heart failure, malignant tumors, severe psychiatric disorders, or recent stroke; (3) history of trauma or ligament injury, or joint replacement surgery within the past six months; (4) severe joint deformity or inability to perform physical activity due to acute symptoms; (5) pharmacological or physical therapy for knee osteoarthritis within the past month; (6) regular exercise programs (≥30 min per session, ≥3 times per week); (7) inability to pass the Mini-Mental Status Examination (score < 24); (8) inability to walk without assistive devices; or inability to communicate in English; (9) pregnancy or plans for pregnancy; (10) participation in other clinical trials within the past 20 days; (11) or plans to relocate during the study period.

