### Recruitment strategies

To recruit participants, we implemented a multifaceted approach that included distributing informational flyers within hospital premises, posting recruitment notices on major social media platforms (e.g., WeChat and Weibo), and placing advertisements in local newspapers and community bulletin boards. We further expanded our reach by screening the patient databases of our hospital's orthopedic and rheumatology departments to identify eligible candidates. Additionally, we partnered with community organizations and established recruitment booths at health expos and senior activity centers to provide detailed information and address inquiries from potential participants.

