While intervention fidelity is rigorously maintained during the initial 12-week supervised phase through standardized protocols and trained instructors, the subsequent unsupervised follow-up period relies partially on participant self-report (e.g., exercise logs). This shift may introduce variability in intervention exposure. We have implemented periodic telephone checks and log reviews to monitor adherence, but the potential for fidelity decay in the long term remains a limitation common to pragmatic trials.

Finally, the external validity of our findings may be constrained by the single-center setting within a specific Chinese hospital and the high frequency of required exercise sessions. These factors may limit the generalizability of results to healthcare systems with different resources or to community-dwelling older adults who may struggle with high-frequency adherence. Our findings should thus be interpreted as the efficacy of these interventions under optimal, supervised conditions. Future research should focus on adapting these protocols for diverse cultural contexts and evaluating their effectiveness in real-world, lower-resource community settings.

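### Exclusion (8) bars anyone unable to communicate in English, which cannot be reconciled with recruiting adults aged 60 or over at one hospital in Zhongshan, China

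*Protocol article*

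**What the plan says.** In the protocol article, Study sample, the exclusion list opens with "Participants will be excluded if they have any of the following", so one item is enough to exclude. Item (8) reads "inability to walk without assistive devices; or inability to communicate in English". The joining word makes the language condition, "inability to communicate in English", stand alone: a person who walks unaided but has no English is excluded.

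The inclusion criteria in the same section set the age ("Participants must be aged 60 years or older") and ask for cognitively intact people "with the ability to communicate effectively through writing or speech". They name no language.

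The end of Study design overview describes the site as "located in Zhongshan, Guangdong, China", and the Discussion calls it a "single-center setting within a specific Chinese hospital". Recruitment strategies lists hospital flyers, "posting recruitment notices on major social media platforms (e.g., WeChat and Weibo", local newspapers, community bulletin boards, the hospital's own patient databases, community organisations, health expos and senior activity centres.

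The article does not state the language of the exercise sessions, lectures, consent or questionnaires, and it gives no reason for an English requirement.

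**The concern.** An eligibility criterion is a binding screening rule, and this one does not fit the trial around it. The site, the age group and the recruitment channels all point to local older adults in a Chinese city. None of the channels is directed at English speakers, and no trial activity is said to need English.

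Site staff therefore have two options, both bad. If they apply the rule, they enrol a selected English-speaking subgroup and may not fill the trial within the planned window. If they set it aside, they enrol people whom the protocol excludes, and a reader of the published criteria will be misinformed about who was studied.

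**Working it through.** The article has no stated figure to reproduce here, because the criterion does not enter the sample-size calculation. The check is mainly textual, with one piece of illustrative arithmetic.

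**Does the criterion operate on its own?** Yes. The list excludes on any item, and within item (8) the language condition follows a semicolon and the word *or*. It is current operative text.

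**Does anything else in the article support or offset it?**

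| Section | What it establishes | Fit with an English requirement |
|---|---|---|
| Study sample, inclusion | Age 60 or over; effective communication, no language named | Neutral: exclusion (8) narrows it |
| Study design overview | One hospital in Zhongshan, Guangdong | Conflicts |
| Recruitment strategies | WeChat, Weibo, local press, community and senior venues, hospital databases | Conflicts |
| Tai Chi, Baduanjin and Health education interventions | Content and frequency; delivery language not stated | No support |
| Discussion, on external validity | Single centre and high session frequency as limits; no language restriction listed | No support |

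The Discussion entry is informative. A deliberate restriction to English speakers at a Chinese hospital would be a major limit on generalisability, and one would expect it to be listed there.

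**What would literal application cost in recruitment?**

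Inputs from the article:
- target N = 120 randomised (Study design overview; Sample size);
- window January to June 2026, six months (Study status and timeline).

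Assumed input: p, the share of otherwise eligible candidates able to communicate in English. The article does not give it, so a range is shown.

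Formulas: candidates needed = N / p; per month = (N / p) / 6.

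| Assumed p | Candidates needed | Per month |
|---|---|---|
| 5% | 120 / 0.05 = 2,400 | 2,400 / 6 = 400 |
| 10% | 120 / 0.10 = 1,200 | 1,200 / 6 = 200 |
| 20% | 120 / 0.20 = 600 | 600 / 6 = 100 |
| 50% | 120 / 0.50 = 240 | 240 / 6 = 40 |
| No language criterion | 120 | 120 / 6 = 20 |

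The criterion multiplies the required pool by 1/p: twofold at 50%, tenfold at 10%, twentyfold at 5%. It excludes more than half of otherwise eligible people whenever p is below 50%.

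**What happens to the analysis if the criterion is ignored?** The Analysis section keeps every participant in the randomised group for the primary analysis. A participant enrolled in breach of (8) therefore stays in. Eligibility is verified before randomisation (Enrollment and the informed consent process), so disregard of the rule would affect all three arms alike and would not by itself bias a between-group contrast. What remains is a set of eligibility deviations and a mismatch between stated and actual population.

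**The case against.** The strongest reply is that this is a drafting or carry-over slip that nobody will follow. Nothing in the article uses or defends an English requirement, and literal application would be noticed at the first screenings. It touches neither the estimand, nor the sample size, nor the type I error. All of that is fair, and it means the article should not be read as showing that the team intends to screen on English. But the article does not mark the phrase as an error, and a rule that staff must disregard in order to run the trial is a defect in the protocol.

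Four stronger readings are tempting, and the article does not support them:

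- *The intention-to-treat population is undermined.* It is not. All randomised participants are kept in their groups, and the breach would not differ by arm. The article plans no per-protocol analysis, so none can be damaged.
- *The exclusion contradicts the inclusion criterion on communication.* It narrows a broader inclusion, as exclusions normally do, and both can be applied together. The conflict is with the site, population and recruitment channels.
- *A definite screening burden follows.* The figures above depend wholly on an assumed p. That most of the target population would be excluded is a plausible inference for this setting, but not something the article states.
- *The registry entry and screening form carry the same error.* Neither is shown, so this is unknown.

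**Conclusion.** The point holds as an error in an operative eligibility rule. Exclusion (8) is irreconcilable with the population, site and recruitment plan that the same article describes, and nothing elsewhere offsets it. Applied literally, it raises the pool of otherwise eligible candidates from 120 to 120/p: from 240 at an assumed 50% up to 2,400 at an assumed 5%, within a six-month window. Ignored, it produces eligibility deviations and a published description that does not match the participants, with no bias to the intention-to-treat comparison from this source.

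The textual conflict needs no assumption about p; only the size of the recruitment problem does. It should be corrected before anyone is screened, because the trial cannot both follow this rule and enrol the population that it sets out to study.

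**What to change.** In Study sample, exclusion (8), replace the English condition with inability to communicate in the language in which the sessions, lectures and questionnaires are delivered at this site. That is presumably Chinese, but the article does not say so. The sponsor should therefore confirm the delivery language and name it. Then check that the registry entry and screening form carry the same wording, and align them if they do not.

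The cost is a one-line amendment. Study status and timeline says that recruitment had not begun at submission and was expected to start in January 2026. Made before the first screening, the change affects no participant and no analysis. Made later, it is a mid-trial amendment, with deviations to document for anyone already enrolled against the rule.

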### Radiographs

Knee radiographs, including anterior-posterior (AP), lateral standing, and sunrise views, are captured during the initial screening phase (baseline assessment) in accordance with the Framingham study protocol (29). These images are assessed by the study's orthopedic expert to identify the presence of a definite osteophyte. If a prior clinical knee radiograph is available and a definite osteophyte can be clearly discerned by the study physician, substitution is allowed, even if the radiograph was obtained using a different protocol.

The weight-bearing knee radiographs are evaluated using the Kellgren-Lawrence (K/L) classification system to assess the overall severity of tibiofemoral joint degeneration. This system assigns a grade to each knee compartment, considering factors such as osteophyte presence, joint space narrowing, and subchondral sclerosis (30). The reported scores reflect the condition of the most severely affected knee, designated as the study knee. Additionally, the radiographs are assessed in accordance with the Osteoarthritis Research Society International (OARSI) atlas, which provides a detailed evaluation of osteophyte size and joint space narrowing in both the tibiofemoral and patellofemoral compartments (31).

